Valid and scientific evidence showing primary operative intervention to be superior compared to closed treatment for dislocated fractures, still lacks [19,20]. Surgery is accepted more and more as primary treatment for dislocated midshaft clavicular fractures, mainly because the results of non-operative treatment are interpreted as inferior to operative treatment [9,15,21,22]. Several studies have examined the safety and efficacy of primary open reduction and internal fixation (ORIF) for completely displaced midshaft clavicular fractures and have noted a high union rate with a low complication rate [23,24,11,9]. However, all these studies were retrospective and only one recent study prospectively compared locking plate fixation with non-operative treatment [9]. In this multicentre, prospective randomised trial 132 patients with a displaced midshaft clavicular fracture were allocated to either operative treatment with plate fixation (n = 67) or non-operative treatment (n = 65). The investigators concluded that operative treatment results in improved functional outcome and a lower rate of mal-union and non-union compared with non-operative treatment after one year of follow-up [9]. One of the important limitations of this prospective randomised trial was a selective loss to follow-up, which occurred predominantly in the non-operatively treated group. This may have obscured the true difference in the outcome parameters between the study groups.

A cost-effectiveness analysis [4] has been performed in this multicentre, prospective randomised trial [9], showing that the cost-effectiveness of ORIF of displaced midshaft clavicular fractures is dependent on the duration and magnitude of functional benefit after ORIF, the disutility before union and increased time to union associated with non-operative treatment, and the actual cost of treatment.

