At each hospital visit various intrinsic (patient-related) and injury-related variables are collected. As part of standard care, X-rays are taken at admission and each follow-up moment. The X-rays are performed in anterior-posterior view and 30° caudocephalad view. After two weeks an X-ray of the contralateral shoulder is taken for comparison with the affected shoulder. The DASH outcome measure and SF-36 are filled out by the patient after two weeks, six weeks, three months and one year. The Constant score of both shoulders is determined after six weeks. The Constant score of the affected shoulder is also determined after three months and one year. The functional tests are performed by a single-blinded researcher or other single-blinded qualified personnel. During these tests, the patients have a sticker on the affected shoulder and they are not allowed to tell the examiner which therapy they have undergone. Furthermore, at each visit the researcher collects medical information according to the follow-up list (i.e., complications/adverse events, secondary interventions). Serious adverse events will be reported directly.

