### Statistical analysis

The research data will be reported following the CONsolidated Standards of Reporting Trial (CONSORT) [26-28]. Complication rates and recovery of function of the shoulder will be compared between the two intervention groups using the Chi-squared test. All other endpoints will be compared using co-variate analysis and student's T-test or Mann-Whitney U-test for, respectively, parametric or non-parametric data. Multivariate linear regression analysis will be performed to model the relation between binary outcome variables and treatment, adjusted for covariates. Data will be presented as mean ± SD (Standard Deviation) for parametric data or medians and percentiles (non-parametric data). P-values lower than 0.05 will be considered statistically significant. The data will be analysed using SPSS version 17 or higher (Statistical Package for the Social Sciences Inc, Chicago IL, USA).

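### Scores measured at three or four visits are compared with single-time-point tests and an undefined covariate analysis, so a one-year comparison ignores what drop-outs scored earlier

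*Protocol article*

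**What the plan says.** **Schedule.** Under Follow-up of patients the article states: "The DASH outcome measure and SF-36 are filled out by the patient after two weeks, six weeks, three months and one year". On shoulder function it states: "The Constant score of both shoulders is determined after six weeks". For the later visits it adds: "The Constant score of the affected shoulder is also determined after three months and one year". Under Outcome measures, strength in six directions is measured from six weeks onwards, which gives three clinic visits.

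**Analysis.** The Statistical analysis section gives four instructions:
- On complications and shoulder recovery, one test is named: "Complication rates and recovery of function of the shoulder will be compared between the two intervention groups using the Chi-squared test".
- On everything else, the instruction reads: "All other endpoints will be compared using co-variate analysis and student's T-test or Mann-Whitney U-test", the choice depending on whether the data are parametric.
- On regression, it says: "Multivariate linear regression analysis will be performed to model the relation between binary outcome variables and treatment, adjusted for covariates".
- On significance, a single rule applies: "P-values lower than 0.05 will be considered statistically significant".

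It names no time point for the repeated scores and no model that links one patient's visits. The abstract adds that analyses follow intention to treat and are both univariate and multivariate.

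**Loss to follow-up.** The sample size section allows for 12% drop-out. The Background describes an important limitation of the earlier randomised trial as "a selective loss to follow-up, which occurred predominantly in the non-operatively treated group", and the Discussion repeats the criticism.

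**The concern.** A t-test or Mann-Whitney test takes one value per patient. Applied at one year, it drops everyone not seen at one year, whatever they scored at six weeks or three months. If loss differs between arms and depends on how recovery was going, the patients who remain are selected differently in each arm and the comparison is biased. This is the weakness the article finds in its predecessor. The earlier scores that would reduce it are already being collected.

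The covariate analysis is not defined, and the one regression that is named is assigned to binary outcomes, so neither clearly covers these scores.

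The significance rule is a second, smaller issue. It is not limited to non-union, to one visit or to one scale per instrument. The Discussion says the treatments will be judged on function, pain, quality of life, cosmetic aspects and complications as well as non-union. A chance finding at one visit could therefore be presented as evidence.

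**Working it through.** **1. Patients left at one year.** From the sample size section: 175 × (1 − 0.12) = 154 per arm. The standard error of a mean difference, in SD units, is √(2/154) = 0.114.

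**2. Bias of a one-year comparison restricted to patients seen.** The article gives only the overall 12%. These inputs are assumed:
- Loss of 18% (sling) and 6% (plate), or 15% and 9%. Each pair averages 12%.
- Standardised three-month and one-year scores, bivariate normal with correlation ρ, and no true treatment difference.
- A log-odds of loss that falls by 1 per SD of a better three-month score.

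Under these assumptions, bias = ρ × (m_sling − m_plate), where m is the mean three-month score among patients still seen at one year.

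| Loss, sling / plate | m_sling | m_plate | ρ = 0.3 | ρ = 0.6 | ρ = 0.8 |
|---|---|---|---|---|---|
| 18% / 6% | 0.157 | 0.056 | 0.030 | 0.061 | 0.081 |
| 15% / 9% | 0.133 | 0.082 | 0.015 | 0.030 | 0.040 |
| 12% / 12% | 0.108 | 0.108 | 0 | 0 | 0 |

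With half the slope, 18% / 6% gives 0.017, 0.034 and 0.046, and 15% / 9% gives 0.009 to 0.023. In these scenarios poor recoverers leave, so the sling group looks better than it is. If good recoverers left instead, the sign would reverse.

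In a simulation of the 18% / 6% case (4,000 runs, 175 per arm), the complete-case bias was 0.031, 0.061 and 0.084 for ρ = 0.3, 0.6 and 0.8. The likelihood-type estimate that uses the three-month score had a bias below 0.005 throughout.

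**3. Precision.** With one earlier value correlated 0.3 to 0.7 with the last one, a joint model raises the effective number at one year from 154 to about 156-164 per arm. This gain is small.

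**4. Number of tests, if every visit were tested.**
- DASH 4 + SF-36 components 2 × 4 + Constant 3 + strength as one measure 3 = 18.
- With six strength directions: 4 + 8 + 3 + 18 = 33.
- With the eight SF-36 domains as well: 33 + 8 × 4 = 65.
- One year only, with six strength directions and the two components: 1 + 2 + 1 + 6 = 10.

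The chance of at least one false positive under independence is 1 − 0.95^k, and the expected number is 0.05k.

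| k | Chance of at least one | Expected number |
|---|---|---|
| 10 | 40% | 0.5 |
| 18 | 60% | 0.9 |
| 33 | 82% | 1.65 |
| 65 | 96% | 3.25 |

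These scales are correlated, so the true chances are lower. For k = 33, correlations from 0.3 within a scale and 0.1 between scales up to 0.8 and 0.7 (assumed) give 78% down to 34%.

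**The case against.** **This belongs in an analysis plan.** Longitudinal models, missing-data handling and multiplicity for secondary outcomes are commonly left to a fuller document, which is not shown. Silence would not be a finding. The article is not silent, however: it assigns tests to these endpoints and sets the significance rule. The point rests on those stated choices.

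**Two-sample tests are not the only methods named.** Correct. Covariate analysis is also named, and if it were defined as a repeated-measures analysis the point would fall. As written it is undefined.

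**Nothing says that earlier data are thrown away.** Also correct. A reader might infer that drop-outs' early scores are discarded. If each visit is tested, those scores are used at the early visits. They only fail to inform the one-year comparison.

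**The bias is small and its inputs are assumed.** This stands in part. The largest value, 0.08 SD, is below the standard error of 0.114 SD. The simulated loss depends on an observed score, which is the condition that favours the likelihood model. If loss depended on unobserved recovery, the model would not be unbiased either. Patients lost before their first scored visit contribute nothing under either method.

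**The test count is a construction.** This stands. The article does not say that every visit, domain and strength direction gets its own test. The domains feed the component scales, and strength is part of the Constant score. A reader might take 96% as near certainty of a spurious result, but that figure needs the maximal count and independence.

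**Conclusion.** The concern holds in a limited form. The methods named for the repeated scores do not include an identified repeated-measures analysis, and a one-year two-sample comparison would not use drop-outs' earlier scores. The resulting bias is about 0.02-0.08 SD with losses of 15-18% (sling) and 6-9% (plate) and correlations of 0.3-0.8. It is about 0.01 SD in the mildest combination tried and nil if loss is equal under the same mechanism. A likelihood-based model removes nearly all of it, provided loss depends on scores already observed. The benefit is real but modest.

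The flat 0.05 rule is a secondary matter. A reader might infer that it undermines the trial's main conclusion. The documents do not support that: non-union is the single primary outcome, the trial is sized on it, and its error rate is not affected by how the secondary scores are tested. Whether to withhold p-values from secondary outcomes altogether is a debatable trade-off, and the point does not depend on it.

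**What to change.** Replace the wording for the repeated scores as follows:
- Analyse DASH, SF-36 component scores, Constant score and strength each with a mixed model for repeated measures on all available visits, with terms for treatment, visit, treatment-by-visit and hospital.
- Name the one-year contrast as the main comparison for each instrument.
- Label other visits and the SF-36 domains as supportive, and report them as estimates with 95% confidence intervals.
- State what the covariate analysis is, or delete the term.

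The uninjured-side Constant score should not be added as a covariate without a plan for missing values. It is taken only at six weeks, so patients who missed that visit would leave the model.

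The cost is analysis wording and slightly more analysis work. No new data are needed, and SPSS, the package named in the article, fits this model. The downside is that an isolated early-visit difference would carry less weight.

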### Ethical considerations

The study will be carried out in compliance with the Declaration of Helsinki on ethical principles for medical research involving human subjects [25]. The Medical Ethics Committee Leiden University Medical Centre (LUMC) acts as central ethics committee for this trial (reference number P10.033 and P10.169; NL31044.058.10 and NL33925.058.10). Approval has also been obtained from the local Medical Ethics Committees of all participating centres. The Medical Ethics Committee LUMC has given dispensation from the statutory obligation to provide insurance for subjects participating in medical research (Medical Research (Human Subjects) Compulsory Insurance Decree of 23 June 2003), because the study concerns two standard treatments and does not introduce extra risks.

## Discussion

The best treatment strategy for dislocated midshaft clavicular fractures remains a topic of debate. Currently, the decision for non-operative or operative treatment of dislocated midshaft clavicular fractures is predominantly based upon the personal preferences of the treating surgeon. In a similar way, when operative treatment is favoured, the type of fixation, intramedullary or (locking) plate fixation, is at the discretion of the surgeon. Research has been done to establish a general consensus on how to treat these types of fractures. The Canadian Orthopaedic Study [9] has provided some insight into how the outcomes after locking plate fixation relate to those after conservative treatment. However, this study has the limitation of a considerable loss to follow-up, predominantly in the non-operatively treated group, which makes it impossible to conclude with certainty that plate fixation is preferred over conservative treatment in active adults. ORIF is most cost-effective for patients who are sensitive to mild functional deficits and strongly value a more rapid return to normal function [4]. Considering these statements, a new randomised controlled trial with sufficient power is needed to provide evidence for a definitive, generally acceptable guideline for the treatment of dislocated midshaft clavicular fractures. The results of this study will help to clarify the question whether plate fixation is superior to non-operative treatment in adults, thereby considering incidence of non-union, functional outcome, pain scores, Quality of Life, cosmetic aspects and complications.

## List of abbreviations used

NTR: Netherlands Trial Registry (in Dutch: Nederlands Trial Register); RCT: Randomized Controlled Trial; ORIF: open reduction and internal fixation; CONSORT: CONsolidated Standards of Reporting Trial; ED: Emergency Department; TenALEA: Trans European Network for Clinical Trials Services; LMWH: Low Molecular Weight Heparin; DASH: Disabilities of the Arm, Shoulder and Hand (DASH) Outcome Measure; HR-QOL: Health-Related Quality of Life; SF-36: Short Form-36; ROM: Range of Motion; MicroFET2: Micro Force, Evaluating and Testing 2; PCS: Physical Component Scale; MCS: Mental Component Scale; SD: Standard Deviation; SPSS: Statistical Package for the Social Sciences; LUMC: Leiden University Medical Centre (in Dutch: Leids Universitair Medisch Centrum);
